## Abstract

**Background:**

Knee osteoarthritis (OA) is considered a major public health issue causing chronic disability worldwide with the increasing number of aging people. In China and increasingly worldwide, many sufferers with knee OA are using complementary and alternative medicine including herbal drug, herbal patch, acupuncture and Tuina etc., to alleviate their symptoms. However, evidence gathered from systematic reviews or randomized controlled trials (RCT) has only validated acupuncture for the management of osteoarthritic pain. Moreover, such Traditional Chinese Medicine (TCM) methods above are commonly used in an integrative way. This trial is aimed to compare the efficacy of an individually integrated TCM approach in the management of knee OA with other single treatments as parallel randomized controls.

**Methods/design:**

Five teaching hospitals will participate in this randomized controlled trial. 500 participants, 100 in each hospital, will be randomly assigned to receive oral administration of a Chinese herbal drug (counter osteophytes capsule), topical use of a Chinese herbal patch (Fufnag Zijin patch), acupuncture, Tuina and the individually integrated TCM approach. The individually integrated TCM approach consists of basic treatment of oral counter osteophytes capsule, variable use of Tuina, acupuncture and a herbal patch based on the severity of the patient's symptoms.

The interventions are given for a period of 4 weeks. The primary outcome measure is the self-reported total score using the Western Ontario McMaster Universities Osteoarthritis Index (WOMAC). Secondary outcome measures include patient and investigator global assessment of response to treatment, patient and investigator global assessment of OA condition, WOMAC pain, stiffness, and physical function subscales, short-form 36 (SF-36) and TCM assessment of OA condition measured by syndromes questionnaire. Mixed models and sensitivity analysis will be used for the statistical analysis.

**Discussion:**

The trial is designed to test the hypothesis that an individually integrated TCM approach is more effective than four treatment modalities used separately. The major limitation of this study is lack of placebo control and of double blinding.

**Trial Registration:**

Chinese Cochrane Center ChiCTR-TRC-00000176

## Background

Osteoarthritis (OA), the most common form of arthritis, is a chronic, degenerative, joint disease that affects mostly middle-aged and older adults. OA is characterized by a series of pathological changes in the whole joint, including cartilage loss, bone remolding, excess synovial fluid secretion, capsular swelling, inflammation in the synovium (synovitis), bone marrow lesions, muscle weakness and atrophy resulting in bone thickening and formation of bone growths or spurs that interfere with joint movement [1,2].

Evidence gathered from a systematic review show that herbal medicines, which appear relatively safe, may offer a much-needed alternative, and merit further attention [3]. Current therapies in China available for the treatment of OA include: oral analgesics such as acetaminophen, ibuprofen, and topicals preparations including both Western medicine and Traditional Chinese Medicine (TCM) products. Acupuncture and Tuina have also been used for the management of OA. Although such TCM methods above have been regarded effective in clinical experiences and case reports, high level evidence has been rarely reported.

Only limited data are available on the efficacy and cost-effectiveness of Traditional Chinese herbs in the treatment of knee OA. According to TCM theory, OA is known as the Bi syndrome (painful obstruction), which means either the limbs or the joints are suffered from pain and malfunction; and herbal therapy has long been a standard treatment. The herbal drug can be used by external application or by oral administration. The counter osteophytes capsule, an extract from Radix Rehamanniae (Dihuang) and Herbal Cistanches (Roucongrong), is a Traditional Chinese herb used for symptomatic treatment of inflammation and pain in osteoarthritis. The earliest report was by Liu who reviewed the effect of counter osteophytes capsule on the treatment of OA in 1,000 cases [4]. Our previous study supported its efficacy in pain management of OA [5].

The Fufang Zijin patch, containing active ingredients extracted mainly from Kadsura Root-bark (Zijinpi) Negundo Chastetree Fruit(Huangjinzi) and Rhubarb (Dahuang), is also commonly used in China for the treatment of OA. According to TCM theory, the Fufang Zijin patch is indicated for the treatment of local joint pain, swelling, numbness, difficulty in physical activities due to the syndrome of "cold-dampness", "meridian obstruction", and "blood stasis".

Tuina is a very important component of TCM together with acupuncture and herbal medicines. Tuina, called 'An Mo' or medical massage in ancient times, usually refers to the doctor using their hands to manipulate the patient's body surface by means of various forms of tuina maneuvers such as pushing, kneading, rolling, wrenching, and flicking-plucking to relax and dredge the meridians and promote Qi flowing and blood circulating. Tuina is considered a natural treatment and manual therapy. It is distinct from chiropractic, osteopathic and mobilization because Tuina is used under the guidance of the basic theory of TCM. Among alternative care consumers with OA, the most commonly used treatment was massage therapy (57%) [6]. Some reports documente similar massage therapy as efficacious in the treatment of OA of the knee [7], but a systematic review of recent trials failed to confirm its efficacy [8].

In many Asian countries and increasing in western countries, acupuncture is a very popular treatment for OA. Systematic reviews and RCTs support the effectiveness of acupuncture for OA pain [9,10].

Optimal management of OA calls for an individual approach based on different constitutions of human body [11]. The individually integrated TCM approach in this study has been formed during 15 years of clinical experience in Shuguang hospital affiliated to Shanghai university of TCM. The approach consists of a basic treatment of orally administered Chinese herbal drugs and varying use of Tuina, acupuncture and herbal patch, all based on the severity of the patient symptoms.

We therefore initiated this study to compare the efficacy of an individually integrated TCM approach, Chinese herb counter osteophytes capsule, Fufang Zijin patch, acupuncture and Tuina in the short-term, symptomatic treatment of OA of the knee. We hypothesized that the integrated TCM approach is more effective than the four treatments, oral medication, topical patch, acupuncture or Tuina, when used alone.

## Methods/design

### Study design

This is a prospective, five-center, parallel-group, randomized controlled efficacy and safety study of individually integrated TCM approach in subjects with knee OA. After giving informed written consent, patients undergo a treatment period of four weeks. Ethics approval was received from Chinese Cochrane Center with the NO:ChiCTRCTET2008-9.

### Participants

All outpatients between 38 and 75 years of age who suffer from painful osteoarthritis of the knee according to American College of Rheumatology (ACR) criteria [12] will be screened. Additional inclusion and exclusion criteria are detailed in Table 1.

**Table 1 T1:** Additional inclusion and exclusion criteria

Additional inclusion criteria	
Pain intensity of 20 mm or more by VAS in the previous 48 hours when walking on a flat surface; At least grade II to III on the Kellgren-Lawrence scale by an X-ray taken within 6 months;	And reluctant to continue on previous drug but willing to change drug treatment.

Exclusion criteria	
Patients presenting with any of the following will be excluded from the study.	

Grade I or Grade IV severity of the index knee based on the Kellgren and Lawrence radiographic criteria as applicable; Use of intra-articular injections or arthroscopy of the index knee within 3 months prior to screening; Evidence of crystalline-induced synovitis in the index knee; History, physical examination, or radiographic results suggestive of acute inflammatory arthritis, rheumatoid arthritis, psoriatic arthritis, septic arthritis, gout, pseudogout, fibromyalgia, systemic lupus erythematosus, or other types of inflammatory arthritis of the index knee; Pain in either knee of neurologic origin;	Signs of clinically important active inflammation in the index knee joint including redness, warmth, and/or a large, bulging effusion with the loss of normal contour at the screening and/or baseline visits; History of acute inflammatory arthritis or pseudogout of the study joint; Cancer/metastatic disease; Systemic or intra-articular corticosteroid use within 60 days of the Screening visit; Known sensitivity to any of the ingredients listed in the treatments under investigation; Significant medical and skin conditions which, in the opinion of the investigator, will interfere with study participation and patch adherence; Replacement of the knee joint.

### Randomization

A total of 500 patients, 100 in each hospital, will be recruited from eligible patients. They will be randomly and blindly assigned to 5 different treating groups through the globally multicentre online randomization facility established by China Academy of Chinese Medical Sciences http://210.76.97.192:8080/cjbyj/.

### Intervention

On Day 0 (Visit 1), patients will begin treatment with either herbal drug, herbal patch, acupuncture, Tuina, or integrative approach. On Day 14, patients will return for an interim visit (Visit 2). On Day 28, the final visit will take place (Visit 3). Thus, the duration of treatment is 4 weeks.

### Oral administration of herbal drug

Participants in this group will receive counter osteophytes capsule (approval NO:Z10980006, manufactured by Jiangsu Kanion Pharmaceutical Co., Ltd) at a daily dose of 5.25 g.

### Topical application of herbal patch

The product, Fufang Zijin patch (approval NO:Z19991106, manufactured by Shanghai LEY's Pharmaceutical Co., Ltd), will be applied at bed time to the right or left knee selected for the study and removed at approximately 8 hours after application (not to exceed 12 hours of exposure time). The location (right or left knee) and time of patch application and removal will be recorded daily in a diary for compliance purposes.

### Tuina

The manipulation will be performed according to established standard operation procedure (SOP) (Table 2).

**Table 2 T2:** Tuina therapy for knee OA

Sequence number	Tuina manipulation
1	The therapist using grasping or rolling applies to the back of the thigh and the crus for 2 minutes.
2	Pushing, kneading or pushing with one-finger meditation on popliteal fossa for 2 minutes.
3	Rolling applies to tensor fascia lata, quadriceps and adductors in the limb for 3 minutes.
4	Rubbing, kneading or pushing with one-finger meditation applies to the Dubi(ST35), Neixiyan(EX-LE5), Ashi points, and each acupoint is about 40 seconds.
5	Gently Pushing the patella to the upward, downward, inward and outward directions for several times, then to the extreme limit of patella and maintaining for 2 and 3 seconds. Repeat 3 times.
6	Pulling the knee. The assistant helps fix the distal thigh, and the therapist uses hands to hold the distal leg and pull for 2 seconds. Repeat 5 times.
7	Passive flexion and extension, adduction and abduction of hip and knee joint to the utmost degree that patient can stand. Repeat 3 times.

Description: The power of tuina manipulation requires evenly and gently application to the degree that patients feel comfort and tolerance. In operations 1 and 2, the patient remains in the prone position. In operations 3 through 7, the patient assumes the supine position.

Dose: about 20 minutes each time and 2 times per week.

### Acupuncture

Acupuncture will be performed according to previously reported SOP [13,14].

### Individually integrated Traditional Chinese Medicine approach

The approach consist of basic treatment of oral counter osteophytes capsule and varying use of Tuina, acupuncture and herbal patch based on the severity of patient's symptoms. The differing individually integrated TCM treatments are shown on the left column of Table 3. The treatment combination (called "approach content" in Table 3) used depends on the WOMAC characteristics as listed in the right column of Table 3. The baseline WOMAC determines the initial treatment, and the ongoing WOMAC later in the trial determines the later ongoing treatments in this arm of the trial.

**Table 3 T3:** Individually Integrated TCM approach for knee OA

Approach content	WOMAC scoring
counter osteophytes capsule	all scoring < 40 mm
counter osteophytes capsule + acupuncture	any one in 5 pain subscales ≥ 40 mm
counter osteophytes capsule + Fufang Zijin patch	any one in 2 stiffness subscales ≥ 40 mm
counter osteophytes capsule + Tuina	any one in 17 physical function subscales ≥ 40 mm
counter osteophytes capsule + acupuncture + Fufnag Zijin patch	both at least one in 5 pain subscales and at least one in 2 stiffness subscales ≥ 40 mm
counter osteophytes capsule + acupuncture + Tuina	both at least one in 5 pain subscales and at least one in 17 physical function subscales ≥ 40 mm
counter osteophytes capsule + Fufang Zijin patch + Tuina	both at least one in 2 stiffness subscales and at least one in 17 physical function subscales ≥ 40 mm
counter osteophytes capsule + acupuncture + Fufang Zijin patch + Tuina	at least one in 5 pain subscales and one in 2 stiffness subscales and one in 17 physical function subscales ≥ 40 mm

Patients in all arms are allowed paracetamol as rescue medication for breakthrough pain at a dose of 500 mg up to a maximum of 2 g per day. The use of rescue medication should not exceed 3 days in each week and should not be taken within 48 hours of a follow up visit. A count of returned tablets will be done at each visit.

### Quality assurance

To ensure that treatments are of a high standard and delivered in accordance with the trial protocol, therapists responsible for application of Tuina and acupuncture will attend a two-day training workshop on the delivery of the treatment programs. They will also be provided with a written protocol and standardized recording documents. In addition, all treatments provided to patients will be carefully recorded. Although patients, investigators, and therapists administering treatment will not be blinded, those assessing the patients for primary and secondary endpoints will be blinded to patient treatment assignment. The investigators, therapists and assessors are different people.

### Endpoints

The primary efficacy endpoint of the study will be Western Ontario and McMaster Universities Index of OA (WOMAC) [15] total score at Day14 and Day 28.

Secondary efficacy endpoints are : i) patient global assessment of response to treatment; ii) patient global assessment of OA condition; iii) WOMAC pain, stiffness, and physical function subscales; iv) investigator global assessment of response to treatment; v) investigator global assessment of OA condition; vi) TCM assessment of OA condition measured by syndromes questionnaire (Table 4); vii)SF-36 assessment.

**Table 4 T4:** Syndromes questionnaire for TCM assessment of knee OA condition

Tongue color (choose one with √ or note for others)					
pale tongue □ pale red tongue □	red tongue □		teeth-marked tongue □	others (please note)	

Tongue fur (choose one with √ or note for others)					

white fur □ yellow fur □	thin fur □		thin fur □	others (please note)	

Pulse diagnosis (choose one with √ or note for others)					

floating pulse □ sunken pulse □ slow pulse □	rapid pulse □ fine pulse □		slippery pulse □ string-like pulse □	others (please note)	

Knee joint situation (mark with √ for yes or no)					

morning stiffness	no □	yes □	cold pain	no □	yes □
pain of unfixed location	no □	yes □	stabbing pain	no □	yes □
joint swelling	no □	yes □	muscle atrophy	no □	yes □

Whole body situation (mark with √ for yes or no)					

easy to sweat at daytime	no □	yes □	easy to sweat at nighttime	no □	yes □
sloppy stool	no □	yes □	hard bound stool	no □	yes □
dry mouth	no □	yes □	profuse dreaming	no □	yes □
reddish yellow urine	no □	yes □	frequent urination	no □	yes □
vexing heat in the extremities	no □	yes □	poor libido	no □	yes □
deafness	no □	yes □	torpid intake	no □	yes □
dizzy vision	no □	yes □	tinnitus	no □	yes □
lack of strength	no □	yes □	somnolence	no □	yes □
lassitude of spirit	no □	yes □	inability to sleep	no □	yes □

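### Two secondary endpoints are named as investigator ratings, yet the plan says investigators are unblinded, are not the assessors, and that secondary endpoints are assessed blind

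*Protocol article*

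**What the plan says.** The Quality assurance section makes three statements about roles:

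- On who knows the allocation: "Although patients, investigators, and therapists administering treatment will not be blinded".
- On who does not: "those assessing the patients for primary and secondary endpoints will be blinded to patient treatment assignment".
- On overlap between the roles: "The investigators, therapists and assessors are different people".

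The Endpoints section then lists seven secondary efficacy endpoints. The fourth and fifth are "iv) investigator global assessment of response to treatment; v) investigator global assessment of OA condition". The Abstract uses the same investigator label. The Efficacy analysis section applies to the investigator rating of OA condition the same repeated-measures mixed model as for WOMAC. It treats the investigator rating of response in a similar way, without the baseline covariate and its interactions.

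Two further statements bear on the scope of the blinding claim. The Abstract says "The primary outcome measure is the self-reported total score" of the WOMAC. The Discussion names the absence of double blinding as a limitation and gives the blinding of the assessing clinicians as a way to reduce bias.

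**The concern.** The five arms differ visibly, so patients and treating staff will know the allocation. A rating by a clinician who does not know it is one of the few safeguards open to such a trial, and the article says that this safeguard covers the secondary endpoints. But two of those endpoints carry the name of a role that the same article calls unblinded and keeps separate from the assessors.

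If sites follow the endpoint names, unblinded investigators will complete the two ratings, and the report may then present them as blinded. Readers would credit them with a protection they did not have. A similar over-reading is possible for the primary endpoint: the blinding statement mentions it, but its values come from the patient.

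**Working it through.** No formula or stated figure is involved. The check is who rates each endpoint and whether that person is blinded.

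**Step 1: the roles (Quality assurance).**
(a) Investigators are unblinded.
(b) Assessors of the primary and secondary endpoints are blinded.
(c) No investigator is an assessor.

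**Step 2: the endpoints (Endpoints, Abstract, Efficacy analysis).**
(d) Endpoints iv and v are secondary efficacy endpoints, named as investigator ratings.

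**Step 3: combine them.** If the name in (d) identifies the rater, then by (a) the rater is unblinded and by (c) is not an assessor, so (b) is false for iv and v. If (b) is true for iv and v, the rater is a blinded assessor, who by (c) is not an investigator, so the name in (d) is wrong. One of the two must give way.

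**Step 4: does the grammar offer a way out?** In "Although patients, investigators, and therapists administering treatment will not be blinded", the words about giving treatment could be read as qualifying investigators as well as therapists, which would leave room for other, blinded investigators. Statement (c) closes that room, because it separates investigators from assessors without qualification.

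**Step 5: tally by named source.**

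- Primary, WOMAC total: the patient (self-reported), unblinded.
- i and ii, "i) patient global assessment of response to treatment; ii) patient global assessment of OA condition": the patient, unblinded.
- iii, WOMAC subscales: the patient, being parts of the same self-reported instrument, unblinded.
- iv and v: the investigator by name, unblinded by (a), but blinded by (b).
- vi, TCM syndromes questionnaire: rater not stated. Table 4 includes tongue and pulse findings, which call for an examiner.
- vii, SF-36: who completes it is not stated.

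So 2 of the 7 secondary endpoints are caught in the contradiction. Counting i to iii as well, 3 + 2 = 5 of 7, and the primary, come by name from someone the plan calls unblinded. For the primary and i to iii this is a matter of describing the blinding accurately. A blinded person who hands over a form does not blind the patient who fills it in.

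**The case against.** The strongest reply is that investigator global assessment is only the customary name of a scale. The Endpoints section lists names and does not assign forms to people. The blinding statement covers all secondary endpoints, and the Discussion calls the blinded raters clinicians, so a blinded clinician may well be meant to complete these two. The article is also condensed, and the full protocol may name the rater. This reading is possible, and it is why one cannot assert that unblinded investigators will do the rating. It still conflicts with the sentence that separates the roles. The point is not a missing detail but two printed statements that do not fit together.

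Four stronger inferences are tempting and are not supported:

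- *That the article hides the open nature of the primary endpoint.* It does not. It says that patients are unblinded, that WOMAC is self-reported, and that the lack of double blinding is a limitation. The Discussion claims only that assessor blinding decreases bias. A blinded administrator can still limit prompting, so that blinding is not worthless. What remains is that the blinding statement should be worded more narrowly.
- *That even a modest bias would swamp the expected differences.* The Sample size section implies integrated-minus-single differences in WOMAC change of 11 − 10.17 = 0.83 (acupuncture), 11 − 9.34 = 1.66 (patch), 11 − 8.89 = 2.11 (Tuina) and 11 − 12 = −1.00 (capsule). Quoting only the positive ones leaves out a comparator with the opposite sign. More importantly, these are WOMAC figures. The document gives no mean or SD for the global ratings.
- *That iv and v are the only clinician-rated outcomes.* Endpoint vi also contains items that need an examiner.
- *That the investigators expect the integrated approach to win.* The document states a trial hypothesis and nothing about individual expectations.

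**Conclusion.** The point holds as an internal contradiction between Quality assurance and Endpoints. As written, either the blinding claim is false for 2 of 7 secondary efficacy endpoints, or their rater is mislabelled. The conclusion rests on taking investigator to mean the same role in both sections, and the document offers no other meaning.

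The size of any resulting bias cannot be derived from the document. The primary analysis, the sample size and the main hypothesis do not depend on these two endpoints. It should nonetheless be corrected: the ratings are analysed for efficacy, and a plan followed by its named roles would produce unblinded ratings that are reported as blinded.

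**What to change.** 1. Have the existing blinded assessors complete both global assessments, rename them as blinded assessor global assessments in the Abstract, Endpoints and Efficacy analysis sections, and ask patients not to disclose their treatment at the rating.
2. If investigators must rate them, keep the names, label both as unblinded, and exclude them from the blinding statement.
3. In Quality assurance and in the Discussion, limit the blinding statement to items that an assessor rates. Describe the self-reported WOMAC and the patient global assessments as unblinded patient-reported outcomes.

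The cost is wording and a change in who fills in two existing forms. No new staff are needed, since the assessors are already part of the plan. There are two drawbacks. The assessor may know the patient's history less well than the investigator does. And the rating will still depend partly on what an unblinded patient says, so it should be presented as a partial check on the primary result, not an independent confirmation of it.

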OA diagnosis is made based on objective radiological criteria along with excluding inection or gout, and it made using the medical history and physical exam. The WOMAC index is a validated scale that uses 24 parameters to assess OA of the hip or knee with focus on Pain, Stiffness, Physical Function, Social Function and Emotional Function [18,19]. The design of this study is consistent with both global clinical research standards and use of TCM criteria for evaluating efficacy and safety. One important principle guiding TCM therapy is to use drug treatment according to "Syndromes". Syndrome is different from the disease name, since it is a summarized analysis of the symptom data from patients' whole situation using TCM methods. It may not only include local symptoms which are part of the disease but also symptoms from the whole body situation. Given the differences in the whole body situation in different people, it is natural that OA, a kind of disease, has different Syndromes. In TCM, OA is known as Bi, Wei, Ganshen kuixu, or Jinmai yuzhi Syndrome and so on [20].

WOMAC questionnaires are detailed in the description of local symptoms of OA, while the Syndromes questionnaires more emphasizes the body's whole situation. Thus, the result of this research could also provide information on the correlation of symptoms-analysis gathered from WOMAC and Syndromes of TCM in different phases (mild, moderate or severe) of OA which may be helpful for predicting severity of OA using TCM methods.

Given the use of two manipulative methods (acupuncture, Tuina) in this study, patients' compliance and response to treatment is critical to the treatment effect. WOMAC subscale analysis will provide information on which OA symptom (pain, stiffness, or function) was more responsive to which treatment. Since this is an East meet West study, outcome measures capture both OA symptoms and the whole body TCM assessment according to TCM theory. We also include a standard quality of life measure, the SF-36, as in many other OA trials [21,22].

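### Three single-choice items of the TCM syndromes questionnaire (tongue colour, tongue fur, pulse) ask for one tick among options that can be present together, and thin fur is printed twice

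*Protocol article*

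**What the plan says.** The Endpoints section of the protocol article lists seven secondary efficacy endpoints. The sixth is "TCM assessment of OA condition measured by syndromes questionnaire (Table 4". Table 4 prints the form itself, with three kinds of item.

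- **Single-choice items (3).** The headings are "Tongue color (choose one with √ or note for others", "Tongue fur (choose one with √ or note for others" and "Pulse diagnosis (choose one with √ or note for others", each with a free-text field for anything else.
  - Tongue colour offers pale, pale red, red and teeth-marked.
  - Tongue fur begins "white fur □ yellow fur" and continues with thin fur, printed twice.
  - Pulse begins "floating pulse □ sunken pulse □ slow pulse" and continues with rapid, fine, slippery and string-like.
- **Knee items (6).** These come under "Knee joint situation (mark with √ for yes or no".
- **Whole-body items (18).** These are also yes/no.

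The Quality assurance section says that those who assess the primary and secondary endpoints are blinded to treatment.

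**The concern.** A single-choice item works when its options exclude one another. In these three items they do not: each puts two or three different attributes in one list and asks for one answer. An assessor who sees two listed features has to choose which to record, and the printed form gives no rule for the choice. Two assessors, or one assessor at two visits, can enter different answers for the same unchanged patient. The tongue and pulse part of the endpoint would then contain apparent changes that are only changes in recording habit. With five hospitals contributing 100 patients each, habits may also differ between sites.

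Timing matters as well. A scoring rule can be written later, but it can use only what the form captured. If the assessor ticked white, the thickness of the fur was not recorded.

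**Working it through.** No sample size, power or error-rate figure bears on this point, and the article states no figure to reproduce. The check is an item count and a reading of the options in Table 4. Sorting the options by attribute follows the plain meaning of their names.

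**Item count**

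- Single-choice 3 + knee yes/no 6 + whole-body yes/no 18 = 27 items.
- Items with overlapping options: 3/27 = 11%.
- Items with a repeated option: 1/27 = 4%.
- Yes/no items: 24/27 = 89%.

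**Attributes inside each single-choice item**

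| Item | Options printed (without free text) | Attributes mixed |
|---|---|---|
| Tongue colour | 4: pale, pale red, red, teeth-marked | colour (3 options), shape (1) |
| Tongue fur | 4 printed, 3 distinct: white, yellow, thin (twice) | colour (2), thickness (1, repeated) |
| Pulse | 7: floating, sunken; slow, rapid; fine, slippery, string-like | depth (2), rate (2), quality (3) |

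**What one tick can record for fur.** Take colour as white or yellow, and thickness as thin or not thin. That gives 2 × 2 = 4 states.

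- White and thin: fits white and either of the two thin boxes.
- Yellow and thin: fits yellow and either of the two thin boxes.
- White and not thin: fits white only.
- Yellow and not thin: fits yellow only.

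A tick on white therefore covers two states, as does a tick on yellow, and a tick on thin covers both colours. No single tick identifies a state. A patient whose fur stays white and thin can be entered as white at one visit and thin at the next, and the data would show a change.

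**Pulse.** One tick records one of three attributes and leaves two unrecorded. Tongue colour has the same problem whenever teeth marks are present, because ticking them gives up the colour.

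**The yes/no items.** Each records a symptom or sign as present or absent (for example morning stiffness, joint swelling, inability to sleep). Yes to no is improvement and no to yes is worsening. These items have a direction, but a sign that persists while becoming milder registers no change.

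**The case against.** The strongest reply is that the defect is small and partly covered by the form. Each of the three items allows a written note, so thick fur or a combination could be entered there. The second thin fur looks like a misprint in the article, and the case report form, which is not shown, may be correct. The Discussion also describes a syndrome as a summary of the patient's whole situation, so the items may never be compared one by one.

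Part of this stands. The repeated option may be only a proofing error, so the form must be checked before anyone concludes that the trial's form carries it. The free-text field does give an outlet, but it yields uncoded text, and an instruction to choose one does not clearly allow two printed options to be reported together. A summary judgement made from the form would still rest on whichever attribute was ticked.

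A reader might infer more than the documents support:

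- **That the questionnaire cannot measure improvement.** This fails for 24 of the 27 items, which have a natural direction. Yes/no recording makes them coarse, not invalid.
- **That the endpoint has no score.** The article gives none, but a scoring or syndrome-assignment rule may sit in the full protocol or the SAP, neither of which is shown. Its absence here is not a finding.
- **That the Discussion's interest in "correlation of symptoms-analysis gathered from WOMAC and Syndromes of TCM in different phases (mild, moderate or severe) of OA" conflicts with entry limited to radiographic grades II to III.** Radiographic grade is not symptom severity, and the article does not say which it means. Table 3 provides for WOMAC scores both below and at or above 40 mm.
- **That the whole-body items should lose their efficacy role, or that a count of the six knee signs should replace the endpoint.** The Discussion says the questionnaire is there mainly for the whole-body picture, and nothing in the article supports such a count.

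**Conclusion.** The point holds for three items of one secondary endpoint. As printed, tongue colour, tongue fur and pulse cannot be coded unambiguously, and a recorded change in any of them may reflect the assessor's choice of attribute and not the patient. That is 3 of 27 items in one of seven secondary endpoints. The WOMAC primary analysis and the other secondary endpoints are untouched.

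If assessor blinding holds, the choice of attribute is unlikely to follow treatment. The likely consequence is then noise and lost information, not a shift in favour of one arm.

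The conclusion rests on two assumptions: that the form in use matches Table 4, and that assessors follow the instruction to choose one. If the case report form already separates the attributes, the point reduces to correcting the published table.

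**What to change.** Before data capture, replace the three items with seven, each with one tick:

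1. tongue colour
2. teeth marks (yes/no)
3. fur colour
4. fur thickness
5. pulse depth
6. pulse rate
7. pulse quality

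Check the repeated thin fur against the case report form and correct it, so that fur thickness has a contrasting option. Leave the 24 yes/no items and the endpoint's status as they are.

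The form grows from 27 to 31 items (27 − 3 + 7). The cost is a one-page revision and four more entries each time the form is completed, with no extra visit or assessor.
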